### **13.2 Identifying and analysing variables influencing compliance and adherence during the study period**

Qualitatively the incidence of the different causes of drop-out will be analysed, globally and per centre. We will differentiate between cardiac and medical reason for drop-out and non-medical reasons.

Analysing the differences in compliance and adherence of patients treated with mHealth solutions (intervention) during the study period.

Statistical modelling of adherence and compliance to maximize the continuation of patients on the program and even make possible that guidelines and changes established would be maintained, so that the benefits of the program would be really durable.

The following information will be used for the statistical modelling.

#### End of mCR programme (T1) data:

- Censoring variable: drop-out mCR programme
- Response variable: Follow-up time (months or weeks)
- Predictor variables: in addition to general input data, medical data about the patient evolution can be used.

[figure not shown]

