### **7.9 Follow-up of subjects withdrawn from treatment**

Patients in the study who experience a reintervention and get a new indication for CR will still be tested at 6 months and 12 months according to the original schedule. However, patients participating in the intervention group perceive no mobile telemonitoring guidance anymore. All patients will also be followed on major outcomes; relapse of myocardial infarction, death, PCI and CABG and utilisation of care.

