#### Data Analysis:

- Survival Analysis (Kaplan-Meier tables with descriptive statistics, Log Rank Test to compare survival by groups and Cox Regression to model survival and calculate Hazard Ratios)
- Logistic Regression (to explain drop-out and compliance)

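### The adherence models in SAP 13.2 use one undivided drop-out indicator, so medical and voluntary stops may be mixed; add cause-specific models beside the all-cause one

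*Combined protocol and SAP*

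**What the plan says.** SAP section 13.2 sets up the modelling of adherence and compliance in the mobile programme (mCR). Under the T1 data it names the status variable as "Censoring variable: drop-out mCR programme", with follow-up time as the response. Under Data Analysis it lists Kaplan-Meier tables, "Log Rank Test to compare survival by groups and Cox Regression to model survival and calculate Hazard Ratios", and a logistic regression for drop-out and compliance. No cause-specific model, competing event or rule for deaths is stated.

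The section opens with a descriptive step: "Qualitatively the incidence of the different causes of drop-out will be analysed, globally and per centre". It adds: "We will differentiate between cardiac and medical reason for drop-out and non-medical reasons". That distinction does not return in the model specification. The reason for leaving the programme appears later, in the list of potential predictors measured at T1, next to drop-out from the programme and drop-out from the study.

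Protocol 7.9 deals with patients who have a reintervention and a new indication for rehabilitation. They stay in follow-up, but "patients participating in the intervention group perceive no mobile telemonitoring guidance anymore". Protocol 7.2.2 defines adherence as the number who drop out or complete, without regard to reason. The SAP places its variable definitions in a separate document that is not supplied.

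**The concern.** The stated purpose of the modelling in 13.2 is to keep patients on the programme longer. That calls for knowing who gives up and why. A patient taken off guidance after a reintervention, or one who dies, has not given up. If these stops share one indicator with voluntary stops, the fitted hazard ratio is a weighted mix of two effects. A factor that predicts only illness can then show up as a predictor of poor adherence, and a factor that acts only on voluntary drop-out is pulled towards no effect.

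Listing the reason for drop-out as a predictor does not repair this. A reason exists only for patients who have stopped, so it cannot predict stopping, and drop-out cannot predict itself. Adverse events recorded up to T1 have a related weakness, since an event may be the trigger of the stop.

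At stake is the reading of the adherence results, and any advice drawn from them about whom to support.

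**Working it through.** **What there is to check.** Section 13.2 states no figure, so nothing can be reproduced. The check has two parts: whether the medical/non-medical split reaches the models, and how much pooling could matter.

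**Does the split reach the models?** In order, 13.2 gives the qualitative incidence of causes with the split; then the information for modelling, with one drop-out indicator; then the methods, with no split; then the predictors, with the reason among them. The split stops at the first step. Read literally, a censoring variable would mean that drop-outs are censored. Since the logistic model is meant to explain drop-out, I read it as the event indicator.

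**Inputs for size.**
- Group size 119 and 30% withdrawal, from the sample-size sections (protocol 5.4, SAP 3). 0.30 × 119 = 35.7, taken as 36 stops. This is for scale only: the 30% is the withdrawal allowance for both arms, not a rate of stopping mCR.
- Assumed: a factor present in 30% of patients; hazard ratio (HR) 3 for medical stops and 1 for voluntary stops; medical share of stops from 10% to 50%.

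**Pooled HR.** Let V and M be the voluntary and medical stops. The illness factor raises medical stops by 0.7 + 0.3 × 3 = 1.6, so the reference level is M0 = M / 1.6. Then pooled HR ≈ (V + 3 × M0) / (V + M0).

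| Voluntary/medical, % of patients | V, M | M0 | Pooled HR | Simulated HR | p<0.05 |
|---|---|---|---|---|---|
| 27/3 | 32.4, 3.6 | 2.25 | 39.15/34.65 = 1.13 | 1.12 | 7% |
| 25/5 | 30, 6 | 3.75 | 41.25/33.75 = 1.22 | 1.22 | 9% |
| 20/10 | 24, 12 | 7.5 | 46.5/31.5 = 1.48 | 1.47 to 1.49 | 18 to 22% |
| 15/15 | 18, 18 | 11.25 | 51.75/29.25 = 1.77 | 1.76 to 1.79 | 35 to 40% |

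The last two columns come from 3,000 simulated cohorts of 119 patients per scenario over 26 weeks, with exponential cause-specific hazards and one-covariate Cox fits. Ranges span separate runs. In the last two scenarios a cause-specific model for voluntary drop-out flags the factor in about 4% of cohorts.

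**Dilution of a voluntary effect.** Take a balanced factor with HR 2 for voluntary and 1 for medical stops. If a share m of reference-group stops is medical, pooled HR = 2(1 − m) + m. For m = 10%, 30% and 50% this is 1.9, 1.7 and 1.5. With 36 stops, Schoenfeld power for the pooled model is 49%, 36% and 23%. With medical stops censored it is 50%, 41% and 31%.

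**Opposing effects.** Suppose a factor present in 30% halves voluntary and doubles medical stops, at the 20/10 split. V0 = 24/0.85 = 28.2 and M0 = 12/1.3 = 9.2. Pooled HR = (0.5 × 28.2 + 2 × 9.2)/(28.2 + 9.2) = 32.5/37.4 = 0.87. Simulation gives 0.85 to 0.86, significant in 4 to 5%. The cause-specific model recovers an HR near 0.5 but is significant in only about 15%.

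**The case against.** The strongest reply is that all-cause drop-out is a legitimate outcome here. Protocol 7.2.2 defines adherence without reasons, SAP 13 counts medical variables among those of interest, and a medical stop also ends participation. On that view a medical predictor of drop-out is an intended result. This stands, and it is why the all-cause model should stay. It does not answer the separate question of who leaves by choice, which the SAP raises when it distinguishes reasons.

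A reader might infer that the models count every stop as drop-out. The documents do not show this. The definitions document is missing, programme drop-out and study drop-out are separate variables, and the coding of a stop under protocol 7.9 or of a death is unknown. Nor does protocol 7.7 settle it: it concerns withdrawal from the study.

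A reader might also infer that comorbidity and previous acute coronary syndrome will be reported as causes of non-adherence while motivational factors are masked. The SAP speaks of predictors, not causes. Comorbidity and previous acute coronary syndrome are in the 13.1 list for participation; they could enter 13.2 only through undefined general input data. The 13.2 lists name no motivational variable. In most scenarios the effect is diluted rather than hidden, and the case of opposing effects has no basis in the documents.

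Finally, the shortage of events limits every version of the model, and a cause-specific analysis does not cure that.

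**Conclusion.** The point holds in a limited form. The models in 13.2 have one undivided drop-out outcome, and the section's own distinction between medical and non-medical reasons is not carried into them. Whether this distorts the results depends on how medical stops and deaths are coded and on how common they are; neither is given. Under the assumed illness factor, pooling yields an HR of about 1.1 when 10% of stops are medical, which is minor, and about 1.5 to 1.8 when 33% to 50% are, which is material. These figures illustrate the mechanism and do not predict the trial's results.

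Objective 9 lies outside the eight objectives listed in SAP section 2, and 13.2 attaches no decision rule to the modelling. The primary VO2peak analysis is unaffected. I would label this a cheap improvement.

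**What to change.** In SAP 13.2:

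1. Define programme drop-out, and say how stops under protocol 7.9, other medical stops and deaths are coded. State that drop-out is the event, not the censoring.
2. Keep the all-cause drop-out model.
3. Add two cause-specific Cox models: one for patient-initiated, non-medical drop-out, and one for medical stop, protocol 7.9 stop or death. Each censors the other at its date.
4. Show cumulative incidence by cause with the Aalen-Johansen estimator. One minus Kaplan-Meier for a single cause, with the other censored, would overstate it.
5. Remove drop-out and the reason for drop-out from the predictor list; the reason belongs in the definition of the outcome.
6. Leave the logistic model all-cause, or give it a multinomial outcome. Do not exclude medical stops from it, since that conditions on an event after randomisation.

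The change is to SAP wording only, because the reasons are already collected. The downside is fewer events per cause-specific model and so wider intervals, which should be said when the results are reported.

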#### Data Analysis:

- Survival Analysis (Kaplan-Meier tables with descriptive statistics, Log Rank Test to compare survival by groups and Cox Regression to model survival and calculate Hazard Ratios)
- Logistic Regression (to explain drop-out and compliance)

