### 7.2.2 Training related outcomes

- Adherence (number of drop-out or completed CR) throughout study period.
- Compliance: compliance to usage of the smartphone (percentage of fulfilling the planned exercise sessions with *mCR* for at least half an hour at 5 five days per week) in the intervention group is determined for the period between baseline and 6 months.

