### 7.5 Randomisation, blinding and treatment allocation

At the start of the CR programme, once patients have indicated not to be interested in the regular CR programme, patients will be informed about the study and requested to participate. After receiving written consent from the patient they will be randomised in 1:1 ratio to the intervention group with mobile telemonitoring guidance or the control group with no mobile telemonitoring guidance or other CR programme by means of computerised allocation system applying an algorithm that prevents the care providers or the investigators from predicting the outcome of the randomisation

process. This means that the person, who determines if the patient is eligible, at the time of this decision, is unaware of which group the patient will be allocated to. The patient, care provider and outcome assessor will not be blinded to the intervention itself because of safety concerns.

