### 3. Sample size

In order to assess the effects on sustained physical fitness after participation in the *mCR* programme it was determined that an inclusion of 119 patients per group would be sufficient to examine the aim of this study. This is based on the expected difference in increase in  $VO_{2peak}$  level of 3.0 ml/kg/min at 6 months between the control and intervention group with an estimated standard deviation of 5 ml/kg/min in the intervention group and 6 ml/kg/min in the control group. Assuming 80% power and 5% two-sided significance level ( $\alpha=0.05$ ), the sample size ( $n$ ) required to achieve a probability of 80% of detecting a difference in an increase  $VO_{2peak}$  level between two independent groups is  $n=55$  per randomisation group. Since patients from different centres (countries) will be pooled in the analysis, we will apply an adjustment for dependency of the observations to calculate the sample size, based on an estimated intraclass correlation coefficient (ICC) for the study centres. The ICC is the proportion of the total variance which is between the centers rather than within centres. An ICC of 0.05 is used in the sample size calculations. After adjustment for the ICC the sample size is  $N=83$  per group. Based on 30% withdrawal we aim for a group size of  $n=119$  per randomisation group ( $n=238$  in total). Six centres will participate in the RCT so we will aim at including approximately 40 patients per centre. As this is a cooperative trial, centres may recruit more patients than this recruitment goal. When one centre starts to dominate enrolment however, recruitment might need to be capped. The total sample size ( $n=238$ ) would be sufficient to detect a clinically and physiologically relevant change in peak oxygen consumption, despite a 30% dropout.

[figure not shown]

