### *Health care cost estimation:*

Direct costs for mobile cardiac rehabilitation will be assigned for the intervention group (with telemonitoring guidance), but not for the control group (no intervention). Care utilization based on activities (clinical admission days, emergency and outpatient clinic visits, GP visits for cardiac (related) complaints or issues, radiology/cardio physiology/nuclear and laboratory tests, and cardiac interventions) will be registered at T1 and T2 and collected by monthly telephone calls with the participants between T1 and T2. A price will be assigned to each service and summed up for each patient individually:

|                                   | Mobile CR | control |
|-----------------------------------|------------------|----------------|
| Costs for CR               | Yes              | No             |
| Costs for care utilization | Yes              | Yes            |

Therefore, total costs (= TC) per patient comprise:

1. Costs for telemonitoring guidance (= CCR, only intervention group)
2. Sum of costs for medical services used outside CR (care utilization, = CCU).

Linear mixed models with centre as random effect will test differences between intervention and control group regarding total costs of care utilisation (see also section 5.1).

Additionally, incremental cost effectiveness ratios (ICER) defined as

$$\frac{\text{Total costs mobile CR} - \text{Total costs control group}}{\text{Outcome mobile CR} - \text{Outcome control group}}$$

will be estimated and a 95% confidence interval will be calculated. Outcome refers especially to the change of peak VO2 and Quality of Life (measured by Physical Component Summary Score and Mental Component Summary Score) during the follow-up period.

[figure not shown]

## 12. Study objective 8

Cardiac patients randomised to the *mCR* programme comply with the use of the smartphone (use of the smartphone on at least 4 days per week with a minimum of 30 minutes of activity per day with a total registration of 150 minutes of activity per week during 21 weeks) during the first 6 months of the study.

Descriptive statistics will be utilised to obtain insight in the use of the smartphone during the first six months of the study. Listed below are the parameters that will be determined.

- Total time (in hours) use of physical activity monitor
- Total time (in hours) use of physical activity monitor with light to moderate intensity

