- Total time (in hours) use of physical activity monitor with moderate to high intensity
- Total time (in hours) use of physical activity monitor with high to extreme intensity
- Number of weeks physical activity monitor is used
- Total number of sessions
- Percentage of weeks subject has reached the exercise goal
- Percentage of patients that comply to the exercise goal

Parameters will be summarised in accordance with section 4.6. Summaries will be reported overall and by group.

[figure not shown]

### 13. Study objective 9

One of the main challenges for CR programmes, especially in elderly is to improve participation, adherence and compliance. A significant number of patients refuse or do not follow CR programmes. In this objective the variables (social, psychological, motivational and medical) are identified that could influence participation and adherence. Especially interesting is if new services guide by eHealth solutions (mCR) can improve adherence rates as well as participation rates.

Data from this study is analysed to define the preconditions for sustainable participation, adherence and compliance. Not participating will be defined by screening failure EU-CaRE RCT (see "EU-CaRE and EU-CaRE RCT SAP definitions" document).

The participation rates in all CVD patients that fulfil the inclusion and none of the exclusion criteria, mentioned in section 1.5, and participate in the randomised controlled trial (RCT) are studied. Compliance and adherence, analysing the drop-outs in the RCT is studied. The methodology and statistical methods will be the same used in the other objectives in addition to other suitable approaches related to each specific objective.

For a more homogenous analysis we will study participation in CAD (inclusion criteria 1,2 and 3 of section 1.5) and in each inclusion criteria group.

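### The compliance model in SAP 13.2 is, on its natural reading, a complier/non-complier logistic regression, although a graded weekly measure is already derived; modelling that measure is a cheap improvement.

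*Combined protocol and SAP*

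**What the plan says.** SAP 13.2, which looks for variables that influence compliance and adherence, lists survival analysis (follow-up time, with drop-out from the mCR programme) and "Logistic Regression (to explain drop-out and compliance". No other method there names compliance as its outcome. Structural equation models and cluster analysis are only to be considered, and they are aimed at satisfaction, expectations and adherence.

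SAP 2.8 and 12 define complying by a threshold: use on at least 4 days per week, at least 30 minutes per day, "with a total registration of 150 minutes of activity per week during 21 weeks" in the first 6 months. SAP 12 then lists two summaries that matter here: the "Percentage of weeks subject has reached the exercise goal", which is graded, and the "Percentage of patients that comply to the exercise goal", which rests on a yes/no status. Both serve descriptive statistics only. Protocol 7.2.2 also treats compliance as graded, as the "percentage of fulfilling the planned exercise sessions with" mCR.

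On numbers, SAP 3 holds that "an inclusion of 119 patients per group would be sufficient", and under protocol 7.5 patients who consent are allocated so that "they will be randomised in 1:1 ratio". Only the mCR arm receives a smartphone.

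**The concern.** A threshold at 21 goal weeks codes a patient with 20 goal weeks the same as one with none. The information on how far patients fell short, or by how much they exceeded the mark, does not reach the predictor model, although it is already in the data set.

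The stake is the purpose of section 13.2. The candidate predictors are many: eight laboratory values at T0, body composition, heart rhythm, lung function, symptom classes and medication, then general input data and T1 variables. A logistic model is limited by the smaller outcome class. If few patients comply, or few fail to, real predictors are missed and odds ratios become unstable.

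The point is about the outcome scale of this one model. Where the threshold lies, and how compliance is described, are not in question.

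**Working it through.** **Patients available.** The plan's figure comes from the primary endpoint (SAP 3): difference 3.0, SDs 5 and 6, two-sided 5%, 80% power.

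- Normal formula: (25 + 36) × (1.960 + 0.842)² / 9 = 53.2, so 54 per group. The t-based calculation gives 79.9% power at 54 and 80.6% at 55, so the stated 55 is reproduced.
- The stated 83 after the ICC is taken as given, since that step does not bear on this point.
- "Based on 30% withdrawal we aim for a group size of" 119: 83 / 0.7 = 118.6, so 119.

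The compliance model therefore has at most 119 patients, and about 83 if only completers are used. The documents give no power, compliance rate or effect size for it.

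**Closed-form guide.** If a normally distributed measure is cut so that a share p are compliers, the information kept is φ(z)² / [p(1 − p)].

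| Compliers | Information kept | Equivalent patients of 119 | Power, if 80% on the graded scale |
|---|---|---|---|
| 50% | 0.64 | 76 | 60% |
| 30% or 70% | 0.58 | 69 | 56% |
| 20% or 80% | 0.49 | 58 | 49% |
| 10% or 90% | 0.34 | 41 | 36% |

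For the first row, φ(0)² / 0.25 = 0.159 / 0.25 = 0.64. With 119 patients, a correlation of 0.254 has 80% power. After the cut it becomes 0.254 × √0.637 = 0.203, and artanh(0.203) × √116 − 1.96 = 0.25, which gives 60%.

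The share of goal weeks need not be normal, so this table is only a guide.

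**Simulation.** All settings here are assumptions:

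- 26 weeks per patient; complier = at least 21 goal weeks.
- Beta-binomial weekly attainment with within-patient correlation ρ of 0.25 or 0.40.
- One standardised predictor with a log-odds slope of 0.4 per SD.
- Linear model on the percentage of weeks (robust SE) against a logistic likelihood-ratio test on the cut.

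Power with n = 119 and no drop-out, graded v yes/no:

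| Mean share of goal weeks | ρ = 0.25 | ρ = 0.40 | Gap (points) |
|---|---|---|---|
| 35% | 96% v 52% | 88% v 56% | 44 and 32 |
| 50% | 97% v 79% | 91% v 70% | 18 and 21 |
| 65% | 97% v 88% | 87% v 75% | 9 and 12 |
| 80% | 89% v 80% | 79% v 70% | 9 and 9 |

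Repeat runs at 80% put the gap at about 6 to 10 points. With n = 83 the gap at means of 35% to 65% is 15 to 49 points. Compliers number about 9 to 17 of 119 at mean 35% and 23 to 32 at mean 50%.

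**Effect of the denominator.** Now 30% drop out at random times and all 119 patients stay in the model.

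- Means of 35% to 65%: 85-96% power over weeks on programme and 72-91% over a fixed 26 weeks, against 41-73% for the cut.
- Mean of 80%, fixed 26 weeks: 53% v 51% and 46% v 39%. The gain nearly vanishes.
- Mean of 80%, weeks on programme: 87% v 53% and 74% v 40%.

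A fixed denominator scores every week after leaving as a missed goal, so drop-out is mixed into compliance.

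**The case against.** The strongest reply is that the SAP's own construct of compliance is the threshold. It appears in 2.8, 4.2.2, 12 and 18, and a logistic model of who becomes a complier answers that question directly. A model of weeks reached answers a related but different one, and protocol 7.2.2 counts planned sessions, not weeks. This stands in part. It is the reason to keep the yes/no model as a companion. It does not show that the threshold is the better scale for finding predictors.

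Second, 13.2 never states that the outcome is yes/no. A grouped-binomial logistic model of weeks reached out of weeks available would fit its words and avoid most of the loss. Definitions sit in a separate document that is not available here, and section 13 admits other suitable approaches. That is fair: the binary outcome is inferred. However, it is the natural reading beside a threshold definition, and nothing quoted pre-specifies a graded model.

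Third, a reader might infer that much of the power is lost whatever the compliance rate. The documents do not support that. They give no rate, correlation or effect size, and the simulated gap is modest when attainment is high. The closed-form losses also assume normality, whereas at mean 50% and ρ = 0.40 the simulated distribution is U-shaped.

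Fourth, section 2 of the SAP lists eight objectives. Objective 9 appears only in section 13, with open-ended methods and no decision rule attached.

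**Conclusion.** The point holds as a cheap improvement. On its natural reading, SAP 13.2 reduces compliance to complier or non-complier for the predictor model, while the graded measure it needs is already derived in SAP 12.

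The direction of the loss is consistent across the settings without drop-out. Its size is conditional: with 119 patients, about 6 to 10 points of power at a mean share of 80%, and about 30 to 45 points at 35%. These figures rest on an assumed slope, within-patient correlation, 26-week period and a single predictor. With drop-out, the benefit depends on using weeks on programme, and those runs assume that drop-out is random.

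It would be wrong to read this as a threat to the trial's main result. The analysis is explanatory and confined to the mCR arm. The primary VO2peak comparison, the per-protocol definition and the descriptive analysis under objective 8 do not depend on it.

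**What to change.** In SAP 13.2:

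- Make the main compliance model a graded one: goal weeks out of weeks on programme, by beta-binomial or quasi-binomial regression, or by linear regression on the percentage with robust standard errors. Include centre in the model.
- Define weeks on programme as the weeks until the patient leaves the mCR programme, and leave drop-out to the survival analysis already listed.
- Keep the yes/no logistic model as a companion that matches the SAP's complier definition, and state its outcome explicitly.

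The cost is a short change of text. The percentage of goal weeks is already derived, so no new data are needed; the weeks on programme come from the drop-out timing that the survival analysis uses. There are two small downsides. The main effect is expressed on the weeks-reached scale instead of as an odds ratio for being a complier, and patients who leave early contribute few weeks.
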